**Sample size estimation:**
We anticipate a reduction in the primary endpoint of 15 % in patients with T2D assessed in the Cardio-Metabolic Clinic compared to the standard of care care. With a power of 80% and an alpha value of 0.05.
1306 patients are needed. We anticipate a dropout rate around 10-15% and therefore 1500 patients will have to be included in the study.

**Descriptive statistics**
Flow of participants will be described with a flowchart for group allocation.
Baseline characteristics between the control group/intervention group will be summarized as mean (SD), median (interquartile range) for continuous variables and as counts (percentages) for categorical variables. Differences between the two groups will be compared with a Wilcoxon rank-sum test for continuous variables and Pearsons Chi2/ Fisher's exact test for categorical variables. Missing data will be specified. Study objectives will be analyzed using the intention-to-treat principle.

**Analysis of primary and secondary outcomes**
The primary and secondary outcome will be analyzed using cumulative incidence function for the composite primary outcome as well as each composite secondary outcome.
Furthermore, we will investigate CV cause mortality through Kaplan Meier estimates.

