**Figure 4 - Timeline for the study**

[figure not shown]

Outcomes The primary outcome is the time to the first occurrence of a composite of CV deaths, non-fatal myocardial infarction, non-fatal stroke, and hospitalization for heart failure.

The secondary outcomes are the time to the first occurrence of one of the single components of the primary outcome, and a combination of the single components of the primary outcome to assess the total symptom burden. Additional secondary outcomes will be the assessment of microvascular complications, protocol driven medical changes and a cost-effectiveness analysis of the Cardio Metabolic Clinic. Primary and secondary outcomes and endpoints are shown in the following table:

| **Primary outcomes** | **Primary endpoints** |
| --- | --- |
| To examine whether patients with type 2 Diabetes (T2D) receiving optimal diabetes care in a Cardio-Metabolic Clinic are superior compared to usual care in reducing; incidence of cardiovascular (CV) death, non-fatal acute myocardial infarction (AMI), non-fatal stroke, and hospitalization for heart failure (HF) | Time to the first occurrence of major adverse cardiovascular event (MACE), a composite endpoint consisting of:   - CV death - Non-fatal AMI - Non-fatal stroke - Hospitalization for HF |
| Units of measure: Measured in days. | Time frame: From baseline to 5 years of follow-up (FU). |

| **Secondary outcomes** | **Secondary endpoints** |
| --- | --- |
| To examine whether patients with type 2 Diabetes (T2D) receiving optimal diabetes care in a Cardio-Metabolic Clinic are superior compared to usual care in reducing; incidence of cardiovascular (CV) death, non-fatal acute myocardial infarction (AMI), non-fatal stroke, and hospitalization for heart failure (HF) | Time to the first occurrence of MACE, a composite endpoint consisting of:   - CV death - Non-fatal AMI - Non-fatal stroke - Hospitalization for HF |
| Units of measure: Measured in days. | Time frame: From baseline to 10 years FU. |
| To compare the individual component, CV death, of the primary endpoint in patients receiving optimal diabetes care in a Cardio-Metabolic Clinic versus usual care. | Time to the first occurrence of:   - CV death   (Presumed cardiac condition leading to death. Including: AMI, venous thromboembolic event, malignant arrhythmia, cardiogenic shock, fatal stroke and aorta dissection) |
| Units of measure: Measured in days. | Time frame: From baseline to 5 + 10 years of FU. |

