**Analysis of categorical outcome**
For each supportive categorical outcome, multivariable logistic regression with generalized estimating equations (GEE), allowing analysis of repeated measures, will be applied, including adjustment for baseline factors, which may contribute to the outcome variable. The model will deliver estimated adjusted odds ratio and 95% confidence interval.
Examples of supportive categorical outcomes: de novo/worsening retinopathy, nephropathy, hypertension and hypercholesterolemia.

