**Testing and confounders**
The statistical test will be performed in a hierarchical order according to the succession of the objectives. The p-value will be corrected with the Bonferroni-Holm method.
Potential effect modifiers are: Sex, age, baseline treatment regime, and baseline comorbidities.

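### The primary superiority comparison is given only a within-arm cumulative incidence function. It should be one defined between-arm model, adjusted for prognostic baseline variables the trial already collects

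*Protocol*

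**What the plan says.** The Outcomes table asks whether patients "receiving optimal diabetes care in a Cardio-Metabolic Clinic are superior compared to usual care in reducing" the four MACE components, with time to first MACE from baseline to 5 years as primary endpoint. This is a between-arm question.

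Under Sample size estimation the trial is sized "With a power of 80% and an alpha value of 0.05"; no test is named there, and the sidedness of alpha is not given.

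Under Analysis of primary and secondary outcomes, the outcome "will be analyzed using cumulative incidence function for the composite primary outcome as well as each composite secondary outcome". The only addition is that "we will investigate CV cause mortality through Kaplan Meier estimates".

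Under Testing and confounders, "The statistical test will be performed in a hierarchical order according to the succession of the objectives" and "The p-value will be corrected with the Bonferroni-Holm method". The same section adds: "Potential effect modifiers are: Sex, age, baseline treatment regime, and baseline comorbidities". These variables are not tied to the primary analysis.

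Adjustment appears only for supportive outcomes. The linear mixed model includes the baseline value of the outcome, and the logistic GEE model is described as "including adjustment for baseline factors, which may contribute to the outcome variable", with an odds ratio and 95% confidence interval.

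**The concern.** The most important comparison in the protocol has the least defined method. Baseline tables get named tests (Wilcoxon, chi-square, Fisher), and supportive outcomes get models, one of them with a stated effect measure and interval. The primary endpoint gets an estimator that describes each arm separately. The testing section then orders tests and corrects p-values that the analysis section has not defined.

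The second issue is efficiency. The Baseline visit and Examinations sections collect age, sex, history of heart failure and of ischemic and other vascular disease, creatinine with eGFR, and NT-proBNP. These plausibly predict MACE. Using them in the primary model costs no patients and no new measurements, and the plan as written does not use them.

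**Working it through.** **1. Can the plan's own figure identify the test?** Inputs from Sample size estimation and Randomization: 15% reduction, power 80%, alpha 0.05, 1306 patients, 2:1. No control event rate is given, and the 15% is not labelled relative or absolute, so 1306 cannot be reproduced from stated inputs.
- Time-to-event reading (Schoenfeld, HR 0.85, two-sided): events = (1.960 + 0.842)² / [(2/3)(1/3)(ln 0.85)²] = 7.849 / (0.2222 × 0.02641), about 1338. That exceeds 1306 patients.
- Two proportions, 15% relative, 2:1, two-sided: the result comes within 3% of 1306 only for a control risk of about 54 to 55.5%.
- 15 percentage points absolute: never more than 420 patients.

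The sample size section therefore does not reveal which comparison was meant. Whether 1306 is adequate is a separate matter.

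**2. The sections side by side.**

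| Part of the plan | Between-arm comparison | Baseline adjustment |
| --- | --- | --- |
| Primary objective (Outcomes) | Superiority, required | – |
| Sample size | Power and alpha, test not named | None stated |
| Primary analysis | Cumulative incidence function only | None stated |
| Supportive numerical | Linear mixed model | Baseline value of the outcome |
| Supportive categorical | GEE odds ratio, 95% CI | Baseline factors |
| Testing and confounders | A test and corrected p-value, not defined | Effect modifiers listed, not linked to a model |

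**3. Size of the available gain, simple approximation.** Start from the planned 80% and let the covariates explain a share R² of the variance. R² is an assumption, and the formula is a linear-type approximation that is not exact for a Cox model:

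power = Φ[(1.960 + 0.842)/√(1 − R²) − 1.960]; equivalent N = 1306 × (1 − R²).

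| R² (assumed) | Power | Equivalent N for 80% |
| --- | --- | --- |
| 0.02 | 80.8% | 1280 |
| 0.05 | 82.0% | 1241 |
| 0.10 | 84.0% | 1175 |
| 0.20 | 87.9% | 1045 |

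The gain runs from 0.8 points (80.8 − 80) to 7.9 points (87.9 − 80).

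**4. Simulation with Cox models.** Assumptions, none from the protocol: exponential event times, 25% five-year event risk, prognostic score with SD 0.7 or 1.0 on the log-hazard scale. Design: N = 1500, 2:1, censoring at 5 years, 2000 trials per scenario. The score that generated the data is itself the fitted covariate.

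| HR | Score SD | Unadjusted | Adjusted | Gain (points) |
| --- | --- | --- | --- | --- |
| 0.85 | 0.7 | 27.8% | 30.6% | 2.8 |
| 0.85 | 1.0 | 24.6% | 31.0% | 6.4 |
| 0.75 | 0.7 | 63.8% | 69.2% | 5.4 |
| 0.75 | 1.0 | 57.7% | 70.3% | 12.6 |

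These rows are near a best case. Real covariates measure prognosis with error, N = 1500 ignores the 10 to 15% dropout, and HR 0.75 is not the planned effect. With a noisily measured score, event risks of 15 to 40% and N of 1306 to 1500, the gain was about 0 to 8 points, typically 1 to 5. The smallest gains are to be expected when events are few.

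**The case against.** The strongest reply is that model, effect measure and covariates commonly sit in a SAP, which is not shown, and that an unadjusted comparison of randomised arms is valid. Both parts are right. If the only complaint were that the test is unnamed, it would be missing detail. What remains is that the protocol does fix a method for its primary endpoint, and a better one is available from data already planned.

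A reader might infer several stronger claims that the document does not support.
- *The plan yields no p-value.* Testing and confounders plans a test and a corrected p-value. The test is undefined, not absent.
- *The plan loses power.* Nothing in the sample size section assumes adjustment, so an unadjusted analysis falls below no stated figure. It leaves a gain unused.
- *The unadjusted hazard ratio is biased toward 1.* Marginal and conditional hazard ratios differ because the hazard ratio is non-collapsible. They are different estimands.
- *Gray's test would be wrong.* The protocol names no such test, and subdistribution and cause-specific analyses answer different legitimate questions.
- *Myocardial infarction, stroke and heart failure alone have no method.* The analysis sentence opens with the secondary outcome in general and ends with the composite ones. It is ambiguous, and it does not clearly exclude the single components.
- *The contrast will be chosen after the data are seen.* Nothing in the protocol says so.

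**Conclusion.** The point holds in a limited form. The primary between-arm superiority question is given an unadjusted within-arm estimator, while other sections presuppose a test, and adjustment is stated only for supportive outcomes. The resulting analysis would be valid once a test is attached, so this is an improvement that should be made and not an error that invalidates the trial.

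The forgone gain is roughly 0 to 8 power points, typically 1 to 5. It rests on assumed five-year event risks of 15 to 40% and moderate prognostic strength; the protocol gives neither. That the present wording leaves the primary comparison undefined depends on no assumption.

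**What to change.** In Analysis of primary and secondary outcomes, state:
- The primary comparison is a Cox cause-specific hazard ratio, Cardio-Metabolic Clinic versus control, with 95% CI and a two-sided test at 0.05.
- It is adjusted for a short list fixed before data are seen, for example age, sex, baseline heart failure, prior atherosclerotic disease, eGFR and log NT-proBNP, with a simple rule for missing baseline values.
- The same model applies to each single component, which removes the ambiguity there.
- The cumulative incidence function, with non-CV death as competing event, is kept for display and for the 5-year risk difference.

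Testing and confounders should then refer to this test, and the sample size section should name the comparison it was based on.

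The cost is wording only. No new data are needed, and 1306 and 1500 are unaffected. The downsides are that the covariate list and missing-value rule must be settled in advance, and that the adjusted hazard ratio is a conditional estimate and should be reported as such. A subdistribution model would also be defensible if preferred; one model should be chosen and stated.

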| To compare the individual component, non-fatal AMI, of the primary endpoint in patients receiving optimal diabetes care in a Cardio-Metabolic Clinic versus usual care. | Time to the first occurrence of:   - Non-fatal AMI   Including: ST-elevation myocardial infarction, non-ST-elevation myocardial infarction |
| Units of measure: Measured in days. | Time frame: From baseline to 5 + 10 years of FU. |
| To compare the individual component, non-fatal stroke, of the primary endpoint in patients receiving optimal diabetes care in a Cardio-Metabolic Clinic versus usual care | Time to the first occurrence of:   - Non-fatal stroke   Including: Thromboembolic or undetermined |
| Units of measure: Measured in days. | Time frame: From baseline to 5 + 10 years of FU. |
| To compare the individual component, de novo HF and/or HF hospitalization, of the primary endpoint in patients receiving optimal diabetes care in a Cardio-Metabolic Clinic versus usual care | Time to the first occurrence of:   - De Novo Heart Failure - Heart Failure hospitalization |
| Units of measure: Measured in days. | Time frame: From baseline to 5 + 10 years of FU. |
| To assess the total symptom burden by a combination of the single component of the primary endpoints in patients receiving optimal diabetes care in a Cardio-Metabolic Clinic versus usual care | Number of overall symptom burden determined by summing the occurrences of:   - CV death - Non-fatal AMI - Non-fatal stroke - Hospitalization for HF |
| Units of measure: Measured in count of events. | Time frame: From baseline to 5 + 10 years of FU. |
| To compare the occurrence of microvascular complication, retinopathy, in patients receiving optimal diabetes care in a Cardio-Metabolic Clinic versus usual care | - Change in diabetic retinopathy stage based on eye examination (Fundoscopy) |
| Units of measure: Measured in ratio to baseline. | Time frame: From baseline to 3 years of FU. |
| To compare the occurrence of microvascular complication, nephropathy, in patients receiving optimal diabetes care in a Cardio-Metabolic Clinic versus usual care | - Change in estimated Glomerular Filtration Rate (eGFR)   Creatinine-based. |
| Units of measure: Measured in in ratio to baseline [mL/min/1.73 m^2]. | Time Frame: From baseline to 3 years of FU. |

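### Kaplan-Meier is fixed for cardiovascular mortality; it censors non-cardiovascular deaths and so overstates the absolute risk of CV death

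*Protocol*

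**What the plan says.** The method is set in two sentences of the protocol, under Analysis of primary and secondary outcomes. The first assigns a "cumulative incidence function for the composite primary outcome as well as each composite secondary outcome". The second reads: "Furthermore, we will investigate CV cause mortality through Kaplan Meier estimates".

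The secondary outcomes table, under Outcomes, makes CV death a time-to-event endpoint of its own at 5 and 10 years. Its objective is a comparison of arms: "To compare the individual component, CV death, of the primary endpoint in patients receiving optimal diabetes care in a Cardio-Metabolic Clinic versus usual care". The event is defined by cause: "Presumed cardiac condition leading to death. Including: AMI, venous thromboembolic event, malignant arrhythmia, cardiogenic shock, fatal stroke and aorta dissection". Deaths outside that definition are not events for this endpoint.

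**The concern.** A patient who dies of cancer or infection cannot later die of a CV cause. Kaplan-Meier for one cause has no place for such a patient except as censored. It then estimates CV death as if that patient could still have died of a CV cause, at the same rate as those who remain alive. One minus the Kaplan-Meier curve describes a population in which nobody dies of anything else, which is not what a reader takes 5- or 10-year CV mortality to mean.

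Three things are at stake:

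- The absolute CV mortality reported for each arm is too high, and more so at 10 years than at 5.
- When non-CV mortality is similar in the two arms, the absolute risk difference is inflated as well.
- CV death is a component of MACE, yet its curve would be on a different scale from the composite's cumulative incidence, so the two could not properly be read side by side.

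**Working it through.** **Inputs from the protocol.** Kaplan-Meier for CV mortality; cumulative incidence for the composites; CV death defined by cause; horizons of 5 and 10 years. The protocol states no CV or non-CV death rate, so it has no figure of its own to reproduce here.

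**Assumptions.** Constant cause-specific hazards: a for CV death and b for non-CV death, each 2% or 3% per year, with no other censoring.

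**Formulas.**

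- What Kaplan-Meier estimates: 1 − exp(−a·t)
- Actual cumulative incidence of CV death: a/(a+b) × [1 − exp(−(a+b)·t)]

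The first exceeds the second for any b > 0, so the direction of the bias does not depend on the assumed rates. Only its size does.

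**Worked case.** With a = b = 0.03 and t = 10, Kaplan-Meier gives 1 − exp(−0.30) = 25.9%. The cumulative incidence is 0.5 × [1 − exp(−0.60)] = 0.5 × 45.1% = 22.6%. As a cross-check, Kaplan-Meier applied to each cause in turn would give 25.9% + 25.9% = 51.8% dead, although only 45.1% die of any cause.

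| CV / non-CV hazard per year | Years | 1 − Kaplan-Meier | Cumulative incidence | Excess, points | Excess, relative |
| --- | --- | --- | --- | --- | --- |
| 2% / 2% | 5 | 9.52% | 9.06% | 0.45 | 5.0% |
| 2% / 3% | 5 | 9.52% | 8.85% | 0.67 | 7.6% |
| 3% / 2% | 5 | 13.93% | 13.27% | 0.66 | 5.0% |
| 3% / 3% | 5 | 13.93% | 12.96% | 0.97 | 7.5% |
| 2% / 2% | 10 | 18.13% | 16.48% | 1.64 | 10.0% |
| 2% / 3% | 10 | 18.13% | 15.74% | 2.39 | 15.2% |
| 3% / 2% | 10 | 25.92% | 23.61% | 2.31 | 9.8% |
| 3% / 3% | 10 | 25.92% | 22.56% | 3.36 | 14.9% |

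Widening the assumed range to 1-4% per year for each cause gives an excess of 0.1-1.6 points (2.4-10% relative) at 5 years and 0.45-5.4 points (5-21% relative) at 10 years.

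**Effect on the comparison of arms.** Take 3% / 3% in the control arm, an assumed CV-death hazard ratio of 0.85 (a = 0.03 × 0.85 = 0.0255 in the clinic arm), and the same non-CV hazard in both arms.

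| Years | Method | Control | Clinic | Risk ratio | Risk difference, points |
| --- | --- | --- | --- | --- | --- |
| 5 | Kaplan-Meier | 13.93% | 11.97% | 0.859 | 1.96 |
| 5 | Cumulative incidence | 12.96% | 11.13% | 0.859 | 1.83 |
| 10 | Kaplan-Meier | 25.92% | 22.51% | 0.868 | 3.41 |
| 10 | Cumulative incidence | 22.56% | 19.57% | 0.867 | 2.99 |

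The ratio is practically unchanged. The risk difference is inflated by 0.13 points at 5 years and 0.42 points at 10 years.

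**The case against.** The best defence is that little depends on this sentence. The stated objective is to compare arms, and the tables above show that the relative comparison barely moves when non-CV mortality is alike. A cause-specific hazard ratio that censors non-CV deaths is a valid contrast in its own right. The primary composite is already assigned a cumulative incidence function. Excluding patients with a life expectancy under 5 years should hold down early non-CV deaths. The analysis sentence opens by mentioning the primary and secondary outcome together, and the Kaplan-Meier sentence opens with a word of addition, so Kaplan-Meier may be meant as a supplement.

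Much of this stands, and it limits the size of the point. It does not remove it. The cumulative incidence sentence narrows to composites, and CV death alone is not one, so Kaplan-Meier is the only method clearly given for it. Even as a supplement, the curve would show absolute risks that are too high. The life-expectancy exclusion cannot be relied on for the 10-year horizon.

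A reader might go further in three ways that the protocol does not support:

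- **That CV death has the most direct competing risk of all the endpoints.** This is doubtful. Non-fatal infarction, non-fatal stroke and heart-failure hospitalization compete with death from any cause, which is a larger hazard than non-CV death alone.
- **That the bias will differ between arms.** It would if non-CV mortality differed, but the document gives no reason to expect that.
- **That the total symptom burden outcome is wrongly given a first-event method.** That outcome is "Number of overall symptom burden determined by summing the occurrences of" the four components, in a count of events. The analysis section never names it. The phrase about composite secondary outcomes already fits 10-year MACE, the kidney composite and the macrovascular composite, which the tables call composite and define by first occurrence. The count method is only left unstated here, and it may be in the statistical analysis plan.

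**Conclusion.** The point holds for CV death. The protocol fixes a method that overstates the absolute risk of a cause-specific secondary endpoint and departs from the approach it takes to the composites in the sentence before. The direction is certain as soon as any non-CV death occurs. The size rests on assumed constant hazards of 2-3% per year for each cause: about 0.5-1.0 points at 5 years and 1.6-3.4 points at 10 years. The inflated risk difference and the nearly unchanged ratio both rest on the further assumption that non-CV mortality is similar in the two arms.

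This is a modest fault in absolute risks, and it matters most at 10 years. It does not touch the analysis of the primary outcome and does not by itself invalidate a relative comparison of CV death. It is worth correcting because the correction is simple.

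**What to change.** Replace the Kaplan-Meier sentence. State that CV death is estimated in each arm with the Aalen-Johansen cumulative incidence function at 5 and 10 years, with non-CV death as the competing event. State that the arms are compared with a cause-specific hazard ratio. Reserve Kaplan-Meier for all-cause death, if that is reported. Showing the cumulative incidence of non-CV death alongside would let readers judge whether it differs between arms.

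The cost is a change of wording. Cause of death already has to be classified for the primary endpoint, so no new data, visits or patients are needed.

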**Analysis of numerical outcome**
For each supportive numerical outcome, we will utilize mixed effects linear regression with included fixed effect for time point and baseline value of the outcome. For each linear mixed effects model, a random intercept will be included for each enrolled patient. These outcomes will be measured at baseline and at 3-year follow-up for the group randomized to drug optimization.
Examples of numerical outcome: changes in biochemistry from baseline to follow-up.

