**Three-year follow-up visit:**
At the three-year follow-up, all participants will undergo the same evaluation program as outlined during the baseline visit. They will be evaluated for clinical events related to the primary and secondary outcomes. Blood- and urine samples will be collected from all participants.

Efforts will be made to ensure that participants attend and complete the three years follow up visit. Participants will receive their appointment for this visit during the baseline visit. Additionally, they will be sent an electronic letter one month before the scheduled follow-up and will be reminded by a telephone call from the study staff.

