## Discontinuation:

Participants will be followed for the complete duration of the study regardless of their adherence to the study intervention. Any component of the study intervention may be discontinued at the discretion of either the participant or the study staff due to safety, behavioral or compliance reasons.

Withdrawal of consent: Participant may withdraw consent at any time upon request. Those considering withdrawal should be offered the option of flexible participation, if feasible. If a participant withdraws consent, any data collected before such a withdrawal of consent may still be used for study purposes. Participants who withdraw will be included as intention-to-treat in the statistical analysis once the study ends.

Lost to follow up: If participants fail to attend and complete the three years follow up visit, they will be considered lost to follow-up for the analysis of the secondary outcomes that requires attendance. However, these participants will still be included in the primary and secondary prognostic outcomes.

Timeline
The study started in January 2024, with a four-year inclusion period that will continue until January 2028. After three years, all patients will have a follow-up visit and baseline assessments will be repeated. Clinical events will be assessed at 5- and 10-years follow-up by journal audits and by look-up in the Danish Health Data Authority. Thus, the 5 years follow-up will be approximately in January 2031, and 10 years follow-up in January 2036 (figure 4).

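### The model for numerical outcomes has no randomised-group term and is worded for one arm only, so it cannot give the clinic-versus-usual-care contrast that the outcomes table asks for

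*Protocol*

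**What the plan says.** Protocol, Statistics, section Analysis of numerical outcome, fixes the model in three pieces:

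- Fixed effects: "mixed effects linear regression with included fixed effect for time point and baseline value of the outcome".
- Random effect: "a random intercept will be included for each enrolled patient".
- Who is measured: "These outcomes will be measured at baseline and at 3-year follow-up for the group randomized to drug optimization".

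Its example of a response is: "Examples of numerical outcome: changes in biochemistry from baseline to follow-up".

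Other sections describe data collection differently. Under the three-year follow-up visit, "all participants will undergo the same evaluation program as outlined during the baseline visit" and "Blood- and urine samples will be collected from all participants". Under Timeline, "After three years, all patients will have a follow-up visit and baseline assessments will be repeated".

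The Outcomes table words each numerical secondary objective (eGFR, UACR, FIB-4, ABI, KCCQ) as a comparison of the Cardio-Metabolic Clinic (CMC) with usual care, from baseline to 3 years. For several of them the unit row reads "Units of measure: Measured in ratio to baseline". Descriptive statistics states that objectives are analysed by intention to treat.

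**The concern.** A model whose only fixed effects are time point and baseline value has no coefficient for the randomised comparison. The sentence naming a single arm makes the omission look intended, because a one-arm model needs no group term. The arm label in that sentence appears nowhere else in the protocol; it presumably means the CMC arm.

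If an analyst follows the text, the result for eGFR or UACR is the mean change in CMC patients over three years. That change contains ageing, regression to the mean and secular change in care as well as any effect of the clinic. It could be reported as an effect of the clinic although the control data that would separate these parts have been collected. The secondary objectives also enter a hierarchical testing order (Testing and confounders), so a p-value from this model would have a formal role.

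**Working it through.** The protocol gives no SD, correlation, drift or power for these outcomes, so there is no stated figure to reproduce. The check compares the passages and then works out what the model estimates. All SDs, correlations, drifts and effects below are assumptions.

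**1. Passages side by side.**

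| Question | Analysis of numerical outcome | Rest of the protocol |
|---|---|---|
| Who is measured at 3 years? | one arm | all participants (three-year visit, Timeline) |
| What is estimated? | time effect, given baseline | CMC versus usual care (Outcomes table) |
| Is there a group term elsewhere? | none listed | none for numerical outcomes; the neighbouring sections cover composites, CV mortality and categorical outcomes |

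**2. What the time coefficient estimates.** Assume SD 1, baseline/3-year correlation 0.6, drift -0.30 in both arms, true CMC effect -0.20, 1,500 patients randomised 2:1, 500 simulated trials.

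- CMC arm only: drift + effect = -0.30 + (-0.20) = -0.50; simulated -0.500.
- Both arms, still without a group term: -0.30 + (2/3)(-0.20) = -0.433; simulated -0.433. This is a pooled change, not a contrast.
- 3-year value on group and baseline, both arms: simulated -0.199 against a true -0.20.

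**3. How often drift alone is significant.** Assume no treatment effect, SD 15, 400 CMC patients and correlation ρ. The SE of the mean change is 15·√(2(1-ρ))/√400. The probability of significance is approximately Φ(|drift|/SE - 1.96).

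| ρ | SE | drift -1 | drift -2 | drift -3 | drift -3, simulated |
|---|---|---|---|---|---|
| 0.5 | 0.75 | 27% | 76% | 98% | 0.978 |
| 0.7 | 0.58 | 41% | 93% | 99.9% | 0.999 |
| 0.85 | 0.41 | 68% | 99.8% | 100% | 1.000 |

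With zero drift the rate is 5%. The planned CMC arm is larger (1,500 × 2/3 = 1,000), which would raise every non-null figure.

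**4. Baseline on both sides (inferred).** With one post-baseline visit, a time effect is estimable only if baseline is a response row, and baseline is also listed as a covariate. If the response is instead the change score, there is one record per patient: time is constant and the random intercept cannot be separated from residual error.

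In the two-row reading with SD 1, the pooled baseline slope is (1+ρ)/2. At ρ = 0.6:

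- residual variance at baseline: (1-ρ)²/4 = 0.04
- residual variance at 3 years: 1 - ρ(1+ρ) + (1+ρ)²/4 = 1 - 0.96 + 0.64 = 0.68
- residual covariance: -(1-ρ)²/4 = -0.04, so the correlation is -0.04/√(0.04 × 0.68) = -0.24

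A negative within-patient covariance puts the random-intercept variance at its zero boundary, as a fitted mixed model confirmed.

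**5. What simple patches would do in that two-row model.**

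- *Group main effect only.* The coefficient averages no effect at baseline with the full effect at 3 years: (0 + (-0.20))/2 = -0.10, half the truth. Simulated: -0.100. Type I error at ρ = 0.5, 0.7, 0.85 is 0.033, 0.039, 0.043, so SEs are slightly too large.
- *Group plus group-by-time.* The estimate is the difference in mean change, which is unbiased. Its true variance factor is 2(1-ρ); the model uses the sum of the two residual variances, (1-ρ)(3+ρ)/2. The ratio is (3+ρ)/4 = 0.875, 0.925, 0.9625, so SEs are about 6%, 4% and 2% too small. Type I error is 2(1-Φ(1.96·√ratio)) = 6.7%, 5.9%, 5.5%; simulated 7.1%, 6.1%, 5.3% (400 and 200 patients).
- *ANCOVA in both arms*: simulated type I error 4.8%, 5.0%, 4.5%.

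**The case against.** The best defence is that the trial plainly means to compare arms: the objectives say so, intention to treat is declared, both arms are measured at three years, and a statistical analysis plan may give the full model. The intent is credible, and control data will exist. But the protocol does not leave the model open. It lists the fixed effects and names the arm, and no other section supplies a group contrast for these outcomes. An analysis plan would have to contradict this text.

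Other objections do stand and limit the point:

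- The double use of baseline is an inference. The text never says that baseline is a response row, and its example of a response is a change. Neither reading gives a coherent model, but the point does not depend on this.
- The 98-100% figure follows from the drift and SD put in. It shows the mechanism and does not forecast this trial.
- A reader might infer that any patch would seriously understate standard errors. That holds only if group enters through the interaction without a main effect, where simulated type I error is about 14-18%. The ordinary model with both terms is only mildly off, and the main-effect patch fails by attenuation.
- A reader might object that a ratio to baseline is undefined for retinopathy stage 0. That does not bear on this model: the section on categorical outcomes assigns worsening retinopathy to logistic regression with GEE.

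**Conclusion.** The section is wrong as written on two counts: it has no randomised-group term, and it restricts measurement to one arm, contrary to the three-year visit and Timeline sections. Followed literally, it estimates drift plus effect (-0.50 for a true effect of -0.20 in the example) and cannot return the contrast defined for eGFR, UACR, FIB-4, ABI and KCCQ. How misleading that would be depends on the unknown drift; the tabulated range runs from 27% false significance at a drift of -1 to 100% at -3, on an SD of 15. The likely double use of baseline is secondary. It matters because quick repairs would either halve the effect or leave type I error around 6-7% in most settings.

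A reader might infer that controls are not assessed at three years, or that the main result is at risk. The documents support neither: sampling covers all participants, and the primary MACE endpoint has its own analysis. This is a should-fix matter for secondary and supportive numerical outcomes.

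**What to change.** In the section Analysis of numerical outcome:

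1. Remove the clause that limits measurement to one arm, and say that both arms are measured and analysed as randomised.
2. Replace the model with: 3-year value regressed on randomised group and baseline value (ANCOVA), all randomised participants of both arms. A two-time-point mixed model with a group-by-time term, and baseline only as a response, targets the same contrast. Constraining the arms to a common baseline mean makes it the counterpart of ANCOVA.
3. For continuous outcomes that the table declares as a ratio to baseline (UACR, for example), analyse log values, so that the group effect is a ratio of geometric means on the declared scale.

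The cost is an amendment of wording. No visit, sample or patient is added, because the protocol already plans these measurements in both arms. It should be done before the 3-year data are analysed.
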